**LIST OF ABBREVIATIONS**

ACOG – American College of Obstetricians and Gynecology

WHO– World Health Organization.

NICU – Neonatal Intensive Care Unit.

GAGs– Glycosaminoglycan.

RCT– Randomized Clinical Trial.

IUFD– Intrauterine Fetal Demise.

ICU – Intensive Care Unit.

IUGR – Intrauterine Growth Restriction.

KNH – Kenyatta National Hospital.

USA– United States of America.

**ABSTRACT**

The World Health Organization (WHO) defines induction of labor as the initiation of labor by artificial means prior to its spontaneous onset at a viable gestational age with the aim of achieving vaginal delivery in a pregnant woman with intact membranes. Successful labor induction leads to vaginal birth while failed induction is the inability to achieve more than 3 cm cervical dilatation after 24 hours of induction of labor. In developed countries, up to 25% of term deliveries involve induction of labor compared to about 9.6% in the developing countries (6). Failed induction is an expected outcome of induction of labor. Combination methods of induction of labor may reduce the high failed induction rates reported by misoprostol or Foley catheter balloon alone.

In this study we propose a randomized trial whose aim is to find out if combined methods have a higher success rate.one arm will utilize misoprostol alone and the other combined misoprostol with Foley’s catheter. The outcomes will include successful induction, maternal and early neonatal outcomes. Failed induction or prolonged duration of induction to delivery may increase costs, patient anxiety, and if not monitored well especially in the setting of heavy workload may lead to poor neonatal outcomes.

If induction of labor using combined Foley and misoprostol can reverse or reduce these outcomes then it can change guidelines on induction of labor or for those patients at risk of failed induction.

A similar study has also not been carried out at our study setting.

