**Introduction**

INDUCTION OF LABOUR

Induction of labor is a procedure used to stimulate uterine contractions during pregnancy before spontaneous labor. Successful labor induction leads to a vaginal birth. A health care provider might recommend labor induction for various indications, primarily when there's concern for a mother's health or a baby's health. In developed countries, up to 25% of all deliveries at term now involve induction of labor. In developing countries, the rates are generally lower, but in some settings they can be as high as those observed in developed countries,(World Health Organization, WHO(3)

Induction of labor is not risk-free and many women find it to be uncomfortable. With a view to promoting the best known clinical practices in labor and childbirth and to improving maternal outcomes worldwide, WHO has developed the present recommendations using the procedures outlined in the *WHO Handbook for guideline development(3)*

General principles related to the practice of induction of labor

Induction of labor should be performed only when there is a clear medical indication for it and the expected benefits outweigh its potential harms.

In applying the recommendations, consideration must be given to the actual condition, wishes and preferences of each woman, with emphasis being placed on cervical status, the specific method of induction of labor and associated conditions such as parity and rupture of membranes.

Induction of labor should be performed with caution since the procedure carries the risk of uterine hyper stimulation and rupture and fetal distress.

Wherever induction of labor is carried out, facilities should be available for assessing maternal and fetal well-being.

Women receiving oxytocin, misoprostol or other prostaglandins should never be left unattended.

Failed induction of labor does not necessarily indicate caesarean section.

Wherever possible, induction of labor should be carried out in facilities where caesarean section can be performed.

The indication for induction of labor therefore must be convincing, compelling, consented to and documented. These conditions are not met when the proposed indication is solely for the convenience of the physician or the woman alone.

Specific recommendations for induction of labor

1. Induction of labor is recommended for women who are known with certainty to have reached 41 weeks (>40 weeks + 7 days) of gestation.

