7-The combination of balloon catheter plus oxytocin is recommended as an alternative method of induction of labor when prostaglandins (including misoprostol) are not available or are contraindicated.

8-In the third trimester, in women with a dead or an anomalous fetus, oral or vaginal misoprostol are recommended for induction of labor.

9- Sweeping membranes are recommended for reducing formal induction of labor.

MANAGEMENT OF ADVERSE EFFECTS ASSOCIATED WITH INDUCTION OF LABOUR

Betamimetics are recommended for women with uterine hyper- stimulation during induction of labor. Uterine hyper stimulation is defined as either occurrence of uterine contractions lasting more than 60 seconds, or occurrence of more than four contractions within 10 minutes, regardless the state of the fetus.Terbutaline is the main beta mimetic used.Tocolytics like magnesium sulfate,atosiban and nitroglycerin have a small effect(3).

Setting for induction of labor

Outpatient induction of labor is not recommended for improving birth outcomes. This because induction of labor requires facilities for monitoring maternal and fetal well-being. Secondly induction should be done in a facility which has the capacity of doing a cesarean section(3).

**DEFINITION OF FAILED INDUCTION**.

Failed induction is defined as labor not starting after one cycle of treatment or after 24 hours. If induction fails, healthcare professionals should discuss this with the woman and provide support. The woman’s condition and the pregnancy in general should be fully reassessed, and fetal wellbeing should be assessed using electronic fetal monitoring. If induction fails, decisions about further management should be made in accordance with the woman’s wishes, and should take into account the clinical circumstances. The subsequent management options include: a further attempt to induce labor (the timing should depend on the clinical situation and the woman’s wishes) or caesarean section.(7). A study done by Osaheni Lucky et al. (Nigeria, 2014) found out 24.1% rate of failed induction. Locally, a study done by Esiromo (KNH, 2011) found out 26% rates of failed induction. The study also found out 77.7% success rate with misoprostol alone and 40% success with Foleys catheter alone.

**Predictors of successful induction of labor**.

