**Outcomes**

Primary outcome-failed induction

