**Sample size calculation**

A recent Kenyan study placed failed induction at 26%.

We postulate that offering a combined use of misoprostol and Foley catheter will reduce this proportion to 16%.

Therefore for us to detect a 16% difference in the successful induction following the use of Foley with misoprostol versus misoprostol alone, we estimated using the sample size formula,

Sample size formula

[Allan Donner; Stat. Medicine (1984)

that we would need to study a total of 180 women (90 per group) to achieve a 80% power to detect the stated difference of 16% at a two-sided alpha=0.05 level of significance.

Where we define p_c_=74% and p_a_=90% to be the proportions of women in the misoprostol and combined misoprostol and Foley groups respectively

and = (p_C_ + p_a_)/2 ( =1.960, and =0.84

**Data collection, management and analysis**.

Data collection and storage: Data will be collected by use of questionnaires by the principal investigator and 3 or 4 well trained research assistants. Information will be obtained from history, review of medical records and clinical examination. The information will be stored safely in a password-protected computer and backed up on a dedicated USB drive. Any hard copy records carried for analysis will be stored under lock and key and patients confidentiality will be observed. A qualified statistician will do analysis as per protocol with intent to treat analysis using SPSS version 21.Primary outcome will be failed induction/successful induction and secondary outcomes include time to delivery, maternal and perinatal outcomes. Proportions will be compares using Chi2 test, 95% CI, two tailed hypothesis with p significant at <0.05

Ethical considerations.

- Permission will be sought from the KNH/UON ERC.
- Informed Consent.
- Confidentiality.
- Patients who decline to give consent will be treated as per the existing protocols and no penalty at all.

Study limitations

Non-blinding may have influence patient management

No long-term follow up of mother and neonate for late outcomes

No interim analysis due to resources.

Study timelines

- Proposal presentation-January 2014
- ERC approval and registration-February 2015
- Enrollment-march-September 2015
- Analysis-September-December 2015
- Presentation-December 2015
- Publishing-December-June 2016
- Dissemination of results-June 2016

Study budget

The anticipated expenses during this study include the following-

Buying of Foleys catheters and misoprostol-

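### The primary outcome, failed induction, carries two incompatible definitions, and neither classifies a caesarean done early, at low dilatation and before labour

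*Protocol*

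**What the plan says.** The Outcomes section of the Protocol reads, in full, "Primary outcome-failed induction". It gives no criterion and no time point. The only definitions are elsewhere:

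- **Abstract:** "Successful labor induction leads to vaginal birth while failed induction is the inability to achieve more than 3 cm cervical dilatation after 24 hours". For failure, this is a dilatation threshold read at 24 h.
- **Definition of Failed Induction (within the Introduction):** "Failed induction is defined as labor not starting after one cycle of treatment or after 24 hours". This is a labour-onset test with no dilatation threshold, and a cycle is not defined.

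Success has no criterion of its own. The Introduction says only "Successful labor induction leads to a vaginal birth", and the Abstract says much the same. The Introduction also states "Failed induction of labor does not necessarily indicate caesarean section", and the definition section lists a second induction attempt among the options after failure.

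The analysis text under Data collection, management and analysis says "Primary outcome will be failed induction/successful induction". The sample size section converts a 26% failure rate into a 74% success rate. Mode of delivery is listed separately as a secondary outcome.

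**The concern.** A binary primary outcome has to put every randomised woman into one of two classes by a rule fixed in advance. Here two rules are given that test different things (how far the cervix has opened, and whether labour has begun), and nothing chooses between them. The joint label of failed and successful induction, beside the remark that success ends in vaginal birth, leaves a possible third reading.

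The choice may not be neutral between the arms. The Conceptual framework attributes part of the combined arm's effect to the balloon pressing on the cervix. Dilatation produced mechanically, without labour, would count as not failed under the Abstract and as failed under the definition section, and only the combined arm has the balloon.

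The trial is open label, and the Study limitations accept that this may affect management. If the criterion is not settled beforehand, it can be settled after allocation and outcomes are known.

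**Working it through.** **1. The two definitions side by side**

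| Woman | Abstract (dilatation) | Definition section (labour onset) |
|---|---|---|
| In labour at 24 h, 3 cm or less | Failed | Not failed |
| Beyond 3 cm at 24 h, not in labour | Not failed | Failed |
| Caesarean before 24 h, low dilatation, before labour | No rule | No rule |
| Caesarean before 24 h, low dilatation, labour begun | No rule | Not failed |
| Caesarean at 6 cm, in labour | Not failed | Not failed |

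The first two rows are contradictions. The third is a gap in both tests and the fourth a gap in one. The last row causes no difficulty as long as the outcome is read as failed or not failed.

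**2. The plan's own sample size**

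Inputs from the sample size section: success 74% and 90% (failure 26% and 10%), two-sided alpha 0.05 (z = 1.96), power 80% (z = 0.84), 1:1 allocation. The pooled-variance formula is

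n = [1.96·√(2p̄(1−p̄)) + 0.84·√(p1(1−p1) + p2(1−p2))]² / (p1 − p2)²

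With p̄ = 0.18:

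n = [1.96·√0.2952 + 0.84·√0.2824]² / 0.16² = (1.065 + 0.446)² / 0.0256 ≈ 89.2, so 90 per arm.

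This matches the stated 180 in total. Power at 90 per arm is 80.3%. The expected failures are 0.26 × 90 = 23.4 and 0.10 × 90 = 9, a contrast of 14.4 women.

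**3. What the unclassified group could do (illustration only)**

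Suppose a share s of women in each arm has an early caesarean unrelated to the treatment effect, and all are counted as failures. The failure rate becomes p = p0(1 − s) + s. The women newly counted as failures number 90 × 0.74 × s in the control arm and 90 × 0.90 × s in the combined arm.

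| s (assumed) | Failure, control vs combined | Women reclassified, both arms | Power at 90 per arm |
|---|---|---|---|
| 0 | 26.0% vs 10.0% | 0 | 80% |
| 5% | 29.7% vs 14.5% | 7.4 | 69% |
| 10% | 33.4% vs 19.0% | 14.8 | 59% |
| 20% | 40.8% vs 28.0% | 29.5 | 44% |

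The documents give no value for s. The table also supposes that the 26% excludes such women, and the documents do not say how the cited Kenyan study defined failure. If it already counted them, adding them again counts them twice. The sizes of the two contradictory groups in step 1 cannot be derived at all.

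**The case against.** A reader might infer a stronger charge: that success is defined as vaginal birth, so that success and failure are not complements and some women are both or neither. On that reading a caesarean at 6 cm is neither, and a woman at 3 cm at 24 h who later delivers vaginally is both. The documents do not support this as the main reading. The Abstract and Introduction say where a successful induction leads, not what it is. The trial schema, research question, hypothesis, first specific objective and Outcomes section all name failed induction. Mode of delivery is secondary, and the 74% reads naturally as not failed. With failed or not failed as the two classes, both examples are classified under the Abstract's test. What remains is loose wording: the joint label in the analysis text, and the Abstract's stated interest in a higher success rate.

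It can also be said that the two definitions are closer than they look. Up to four doses 6 h apart span about 24 h once the last interval is included, so the time limits roughly coincide. That is fair and narrows the conflict to the criterion, but it does not remove it.

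The definitions do sit in background text, and a statistical analysis plan may hold detailed rules for early caesareans. But these are the only definitions in the Protocol, and they contradict each other. A contradiction is not detail left for later.

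The objection to the power figures stands. They rest on an assumed share and an unverified premise about the 26%. The 80% starting point is itself open to question, because the sample size section also postulates a fall to 16% failure rather than 10%. That is a separate matter.

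**Conclusion.** The point holds and needs correcting in the Protocol. The primary outcome has two tests that classify some women in opposite ways. Neither handles a caesarean before 24 h at low dilatation and before labour, and the Outcomes and analysis texts do not choose between them. This follows from the text alone and needs no assumption.

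The size of the effect on the result is not known. The power figures show only that the rule for early caesareans could matter beside a planned contrast of about 14 women. They are not an estimate of lost power. That the balloon arm would contain more women dilated without labour is plausible from the Conceptual framework but is not shown by any figure in the documents.

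**What to change.** Reconcile the Abstract, the Definition of Failed Induction, the Outcomes section and the analysis text to one binary definition of failed induction:

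- One criterion (either existing one would serve) and one time point, measured in both arms from the first misoprostol dose and worded identically wherever it appears.
- A stated rule for a caesarean before that time point, so that every randomised woman is classified.
- The term not failed for the complement, in place of successful induction, with vaginal birth kept under the secondary outcome mode of delivery.
- A statement of whether the 26% planning rate was measured on the chosen definition.

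The cost is wording in the Protocol and data forms. If the 26% was measured differently, the planning rate has to be restated and the sample size checked against it.

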**Secondary outcome**

Induction to delivery time

Mode of delivery

Maternal outcomes-PPH, chorioamnionitis,hyperstimulation(5 contractions in 5mins)

Perinatal outcomes (APGAR, NICU admission

Methodology

Block randomization of all eligible consenting subjects by computer generated random sequences and a randomization ratio of 1:1.Upon enrollment, an opaque envelope containing the participant’s enrollment number and assignment to either the Foley plus vaginal misoprostol or vaginal misoprostol alone will be opened .Each participant will be assigned a unique 4-digit-long subject number for subject identity and confidentiality. Participants and health provider will be aware of the treatment allocation at the time of assignment of treatment.

Study procedures.

Patients who fall in the Misoprostol arm will be given 25 mcg vaginally 6hourly up to a maximum of 4 doses, Bishop score >6 or when they go into active labor. Later amniotomy and augmentation may be done as per protocol

Patients who fall in the Combination arm will be inserted an 18-French Foley catheter with a 30 cc balloon will be placed just above the internal cervical os and then inflated with 30 cc of sterile saline. The length of the Foley catheter will be affixed to the subject’s inner thigh under slight tension. At the same time 25 mcg of misoprostol is inserted at the posterior fornix of the vagina 6 hourly up to a maximum of 4 doses, Bishop score >6 or active labor. If difficult, Foley catheter insertion will be attempted every 6 hours unless Bishop score more than 6 or in active labor. When Foley balloon falls off, labor may be augmented or amniotomy performed as per the existing protocol.

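### Failed induction is defined in two ways and the primary outcome selects neither; under the dilatation wording, the balloon could produce non-failures in the Foley arm only

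*Protocol*

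**What the plan says.** The protocol describes success or failure of induction in three ways.

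- **Abstract, by dilatation:** "failed induction is the inability to achieve more than 3 cm cervical dilatation after 24 hours of induction of labor". No contractions, labour or delivery are required.
- **Abstract, same sentence, by delivery:** "Successful labor induction leads to vaginal birth".
- **Introduction, under the heading that announces the definition, by labour onset:** "Failed induction is defined as labor not starting after one cycle of treatment or after 24 hours".

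The Outcomes section says only "Primary outcome-failed induction", with no definition attached.

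The study procedures (under Secondary outcome) give the combination arm alone a balloon. An "18-French Foley catheter with a 30 cc balloon will be placed just above the internal cervical os", and the catheter is then "affixed to the subject’s inner thigh under slight tension". Both arms have the same misoprostol schedule. In the combination arm, augmentation or amniotomy may follow once the balloon has fallen off. The Conceptual framework names local balloon pressure on the cervix as a mechanism in the combination arm only.

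The design is open label: "Participants and health provider will be aware of the treatment allocation at the time of assignment of treatment". No blinded outcome assessment is described. The Study limitations mention non-blinding only as a possible influence on patient management.

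**The concern.** An outcome should measure the same thing in both arms. Under the Abstract's wording it may not. A woman in the combination arm whose cervix has been opened by the balloon could be counted as not failed although labour has not begun. A woman on misoprostol alone has no such route. The error would run in one direction, towards the combination arm.

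The trial hopes to inform guidelines on reducing failed induction, and it links success to vaginal birth. A significant difference made up partly of balloon dilatation would not show that more women went into labour or delivered vaginally. Because the wording determines what is recorded at the bedside, it has to be settled before enrolment. A later analysis may not be able to recover labour onset if it was not collected.

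**Working it through.** **1. The plan's own sample size.** Inputs from Sample size calculation: success 74% and 90%, two-sided alpha 0.05, power 80%, z-values 1.960 and 0.84. The mean proportion is (0.74 + 0.90)/2 = 0.82.

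n per arm = [1.96·√(2 × 0.82 × 0.18) + 0.84·√(0.74 × 0.26 + 0.90 × 0.10)]² / 0.16² = (1.065 + 0.446)² / 0.0256 = 89.2, so 90 per arm.

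The stated 180 is reproduced, with power 80.3% at 90 per arm. That arithmetic is not at issue here.

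**2. Balloon against threshold.** Input: 30 cc, from the study procedures. Assuming a sphere, D = (6V/π)^(1/3) = (180/π)^(1/3) = 3.86 cm. For an elongated balloon with length/width ratio r, the width is (180/(πr))^(1/3):

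| r | width (cm) |
| --- | --- |
| 1 | 3.86 |
| 1.5 | 3.37 |
| 2 | 3.06 |
| 2.2 | 2.96 |

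The width stays above 3 cm up to a ratio of about 2. Passage of the balloon can therefore meet the Abstract's criterion without labour.

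**3. Effect on the test.** Assume true failure of 26% in both arms (the planning rate) and an artefact of d points in the combination arm only. The documents give no value for d. Then p₁ = 0.26, p₂ = 0.26 − d, n = 90 per arm, and

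P(significant, favouring Foley) = Φ[(d − 1.96·SE₀)/SE₁],

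with SE₀ = √(2p̄(1 − p̄)/90), where p̄ is the mean of p₁ and p₂, and SE₁ = √([p₁(1 − p₁) + p₂(1 − p₂)]/90).

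- d = 0.05: p₂ = 0.21, SE₀ = 0.0632, SE₁ = 0.0631. (0.05 − 0.1239)/0.0631 = −1.17, so P ≈ 12%.
- d = 0.10: p₂ = 0.16, SE₀ = 0.0607, SE₁ = 0.0603. (0.10 − 0.1190)/0.0603 = −0.32, so P ≈ 38%.
- d = 0: P = 2.5%, the nominal rate in that direction.

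As a share of would-be failures in the combination arm, these artefacts are 5/26 = 19% and 10/26 = 38%. A smaller share of 10% (d = 0.026) gives P ≈ 6%. To reproduce the whole 16-point difference used for the sample size, the share would have to be 16/26 = 62%.

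**4. The same woman under each definition.** Take a woman who has expelled the balloon, measures more than 3 cm at 24 hours and is not in labour.

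- Abstract, dilatation: not failed.
- Introduction, labour onset: failed.
- Vaginal birth as success: not yet a success.

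The artefact belongs to the first definition and largely disappears under the other two.

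**The case against.** A reader might infer that the primary outcome is biased as it stands. The documents do not support that. The dilatation wording is background prose in the Abstract. The passage actually headed as the definition uses labour onset, and the Outcomes section adopts neither. This objection stands and makes the concern conditional. It does not remove it: nothing in the protocol selects the Introduction's definition, and the Abstract's is the only one with a measurable threshold, so it is the easy one to apply on the ward.

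The size is also unknown. To be misclassified, a woman must expel the balloon, still not be in labour at 24 hours, and still measure more than 3 cm then. Repeated misoprostol, and augmentation or amniotomy after the balloon falls off, both reduce that group. The protocol does not say how or by whom dilatation is measured. The balloon's diameter at expulsion is not the dilatation recorded at 24 hours. All of this stands, and the 5 to 10 points are only an illustration. Nor can they be expressed cleanly as a share of the planned effect, because Sample size calculation gives both a fall from 26% to 16% (10 points) and a 16-point difference.

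Dilatation is also partly what the Foley is meant to achieve, since the research question covers cervical ripening as well as induction. That is fair, but the stated primary outcome is failed induction, not ripening.

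Finally, mode of delivery and induction-to-delivery time are already secondary outcomes, so a gain in dilatation without a gain in delivery could be noticed. This limits the harm but does not correct the primary result.

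**Conclusion.** The point holds in conditional form. The protocol carries conflicting definitions of its primary outcome and selects none. If the dilatation definition is used, misclassification favouring the combination arm is possible, and the protocol describes no safeguard against it. That bias will occur is not shown.

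With true failure of 26% in both arms, 90 women per arm and an assumed artefact of 5 to 10 points, the chance of a significant result for Foley rises from 2.5% to about 12% to 38%. A smaller artefact gives less: about 6% at 2.6 points. The result rests on the assumed artefact, on a roughly spherical balloon (or one no longer than about twice its width), and on the cervix remaining above 3 cm at the 24-hour assessment.

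The sponsor should correct this before enrolment. Reconciling the passages is not sufficient if the reconciled text keeps dilatation alone as the criterion.

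**What to change.** Reconcile the Abstract, the Introduction and the Outcomes section into one primary definition that the balloon cannot satisfy by itself. The protocol already contains a suitable one: labour not having started. State it under Outcomes, assess it by 24 hours from the start of induction in both arms, and write the criteria for labour onset so that dilatation alone does not meet them.

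Do not tie any condition to removal or expulsion of the balloon. Such a condition has no counterpart in the control arm, and it would leave women whose balloon comes out late less time to qualify, which could penalise the Foley arm.

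Make vaginal birth within 24 hours the leading supporting secondary outcome. It can be derived from mode of delivery and induction-to-delivery time, both already listed.

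The cost is a change of outcome wording and possibly one data-form item for labour onset. Two drawbacks remain. Labour onset would still be judged by staff who know the allocation, so the less judgement-dependent delivery outcome matters as a check. The 26% planning rate, and the sample size built on it, must be checked against the definition chosen.
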